### Data management

Original survey forms will be returned to the agency at the end of each round of data collection. A secure courier service that has been assessed to satisfy agency procurement policies will be used to transport the data from schools. Original survey forms will be entered onto SPSS by trained blinded research support staff and subsequently stored in an off-site secure storage facility. During the data entry process all files will be kept in locked office cabinets. Regular checks will be carried out for quality control purposes including range checks, valid values and spot checks against original survey forms. Any modifications to data entered will be recorded in a data entry log. There will be significant investment in establishing and maintaining strong relationships and open channels of communication with school level stakeholders including teachers and parents to ensure that data is collected with process informed consent and within a context that safeguards the welfare of children and prevents harm. A queries log will be used to document and track all concerns or queries raised, and capture learning for data collection across the trial duration. A data monitoring committee will not be required for this trial. The conduct of this trial, including modifications to the protocol (trial registry record to be updated annually), will be monitored via quarterly reporting and meetings with the Department of Education and audit by the Department of Finance and Personnel of the Northern Ireland Executive.

Online data storage will be managed by Snap Surveys Ltd. who are independently audited and certified by Bureau Veritas as being compliant with ISO 27001, the internationally recognised gold standard for information security systems. Snap’s UK and US based data centres are hosted at Rackspace, an ISO 27001 certified organisation running SAS 70 / SSAE 16 certified data centres.

### Planned analyses

The data structure within the study is hierarchical, i.e., occasions are nested within the children at level-1 (occasions and individuals are at the same level because a multivariate approach will be taken to the analysis, where this is practical). Each child is nested within a class (level-2), and these classes are nested within the schools (level-3). Variables appropriate to each level will be used in the analysis. At level-1 change in scores across the stages of assessment will be examined within the context of individual variation within and between individuals and the possible factors that might influence these differences, e.g., level of understanding, social background etc.; at level-2 (classroom) the fidelity to the programme will be examined in the context of its effect on the results.

Data will be initially summarised using frequencies, measures of central tendency and spread. The different constructs (examples) will be analysed in two different ways. Equally weighted summed scores will be used where constructs can be empirically shown using measurement models that can be described as belonging to one dimension. In this event the analysis will proceed within the linear mixed models option in SPSS. This will allow both random and fixed effects to be examined in the context of longitudinal data with missing data handled under the assumption of missing at random [70–73].

A second more rigorous approach will also be taken to the analysis [74]. In this option, a structural equation modelling (SEM) approach will be taken, where the constructs will be evaluated across the three points in time, using tests of factorial invariance. A multigroup approach, within the SEM analysis, will be used to test differences across the conditions.

Clustering at the various levels will be considered through the application of multilevel models, as described above, and in some cases using a sandwich estimator (Huber-White) to take account of the non-independence. In the latter case, an adjustment is made to the standard errors and the chi-square test of model fit. The analyses will be conducted within SPSS, STATA or Mplus. Interim analyses focussed on primary outcomes will be conducted with baseline and time 1 data. The results will be shared with the project funder to inform the Department of Education’s strategic business planning process. Interim results will only be reported to schools once time 2 data collection has ended.

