	8-11yrs. the difference in needs and wants, they have a right to feel safe and secure, how their body reacts when they are angry or feel threatened, what is safe to share online and offline, to tell an adult if they are being asked for personal information online or being asked to meet someone they have met online, what is meant by cyber bullying, how and why it happens and how to deal with it, to educate younger children in the school about ‘Keeping safe’.

The ‘Whole- School’ model adopted by Keeping Safe is increasingly advocated in policy documents [1, 2, 49] yet is relatively untested and lacks evidence of effectiveness [30]. This model supports the development of Keeping Safe as a multi-component programme with key components targeted at children and their parents as well as teachers and other whole school staff.

Teaching and learning resources seek to build the capacity of school staff to teach and reinforce messages through the formal and informal curriculum. These were designed to integrate into the existing ‘Personal Development & Mutual Understanding’ statutory component of the Northern Ireland Curriculum in primary schools and to the wider life of the school [30, 34]. The classroom based materials developed across three themes of healthy relationships, my body and being safe, include a wide range of materials including 63 lesson plans (nine for each class group per year) designed to teach key messages incrementally as the children progress through the 7 years of their primary school education from Primary one to Primary seven. This approach of providing curriculum support materials that are tailored to the age and developmental abilities of the children and build on prior learning is associated with effective prevention programming [29, 30, 48]. In practice, school leaders will deliver a prepared assembly, one of twelve available, to introduce the theme for the term. Each teacher will then deliver three age appropriate lessons to their class and ask the children to complete the accompanying homework with their parents or carers. The structured programme provides teachers with sufficient time and multiple opportunities to revisit and reinforce key messages; important elements of effective programmes [48].

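### The stated hierarchy gives each child one class across assessments spanning two years, although class, teacher and fidelity are year-specific, and the plan does not commit to school and class effects that vary by occasion.

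*Protocol article*

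**What the plan says.** All of the modelling text is in the Planned analyses section of the protocol article.

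- Hierarchy: "Each child is nested within a class (level-2), and these classes are nested within the schools (level-3".
- Occasions: "occasions and individuals are at the same level because a multivariate approach will be taken to the analysis, where this is practical".
- Change: "At level-1 change in scores across the stages of assessment will be examined within the context of individual variation within and between individuals".
- Class level: "at level-2 (classroom) the fidelity to the programme will be examined in the context of its effect on the results".
- Random effects: "This will allow both random and fixed effects to be examined in the context of longitudinal data". Which effects are random is not stated.
- Robust variance: "in some cases using a sandwich estimator (Huber-White) to take account of the non-independence". The clustering level is not named.

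Elsewhere, the Methods section sets assessments at baseline and one and two years later. The Intervention section describes lessons taught incrementally "as the children progress through the 7 years of their primary school education from Primary one to Primary seven", with nine lessons per class group per year, delivered by each teacher to their own class. The Trial design section names the school as the unit of analysis, with individual-level analysis as well that allows for class and school nesting. The Discussion states the hypotheses at T2. No arm-by-time test is written out.

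**The concern.** There are two separate problems.

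First, a child followed from baseline to T2 passes through up to three year groups, usually with a different teacher each time. No single level-2 unit describes that child at all three occasions. The actual structure is child crossed with class-at-occasion, within school. Fidelity is recorded by the teacher of a given year, so with one class per child at least one year's fidelity would be attached to a classroom the child was not in.

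Second, schools were randomised, so the error term for an arm difference in change must include variation between schools (and classes) in change. The plan describes change at level 1 only, and the two devices that could bring in cluster-level variation are both conditional. If class and school were fitted as intercepts constant over time, they would drop out of the T0-to-T2 difference and the arm effect would be judged against child-level noise. The same would apply to the interim T0-to-T1 analysis, whose results go to the funder for business planning.

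**Working it through.** **Does one class per child fit?** Three assessments one year apart, annual progression from Primary one to Primary seven, and nine lessons per class group per year cannot be reconciled with one class per child for teacher or fidelity. This needs no arithmetic. For classmates it depends on whether classes are re-formed. Average enrolment of 200 over seven year groups is 200/7 = 28.6 children per year group, so many schools may have about one class per year that moves up together. The document gives no class counts.

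**What would constant intercepts do?** The plan gives no figure for the variance of change. Its nearest figure, a detectable effect of 0.19 SD, concerns sample size. With 40 schools per arm, ICC 0.2 and 150 surveys per school, the unadjusted formula gives 2.80 × √[(2/40)(0.2 + 0.8/150)] = 0.284; 0.19 would need a baseline R² of about 0.55, which is not stated. That is a separate matter and is not used below.

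Inputs from the Sample size section: k = 40 schools per arm, and m = 150 × 50% = 75 matched pupils per school. Assumptions: q = 5 classes per school, equal in size; per-occasion variances s (school-by-occasion), c (class-by-occasion) and e (child residual, 0.5 or 0.32). For the T0-to-T2 contrast with matched pupils only:

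- True variance = 2 × [2s/k + 2c/(kq) + 2e/(km)]
- Variance reported by a constant-intercept model = 4 × (s + c + e)/(km)
- Type I error = 2 × [1 − Φ(1.96 × reported SE / true SE)]

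Example with s = 0.01, c = 0, e = 0.5:

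- True variance = 2 × (0.0005 + 0.000333) = 0.001667, SE 0.0408.
- Reported variance = 4 × 0.51/3000 = 0.00068, SE 0.0261.
- SE ratio 1.57, type I error 0.21.

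| s | c | SE ratio (e = 0.5) | Type I (e = 0.5) | Type I (e = 0.32) |
|---|---|---|---|---|
| 0 | 0 | 1.00 | 0.05 | 0.05 |
| 0 | 0.02 | 1.24 | 0.11 | 0.15 |
| 0 | 0.05 | 1.51 | 0.19 | 0.25 |
| 0.01 | 0 | 1.57 | 0.21 | 0.28 |
| 0.02 | 0 | 1.96 | 0.32 | 0.40 |
| 0.04 | 0 | 2.55 | 0.44 | 0.52 |

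A simulation with e = 0.5 (4,000 runs per setting) agrees: 0.050 with no cluster variation in change, 0.107 and 0.187 for class-by-occasion variance 0.02 and 0.05 alone, 0.215 for s = 0.01, and 0.341 for s = c = 0.02. In the same runs a school-level analysis of change rejected 0.046 to 0.052 of the time, and a school-clustered sandwich 0.052 to 0.060.

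**The case against.** The strongest reply is that the plan never says school and class enter as constant intercepts. In a multivariate multilevel model the occasions are separate responses, and school and class can each carry a covariance matrix across occasions, so cluster variation in change is estimated. The school is named as the unit of analysis, a sandwich estimator is available, and a second analysis by structural equation modelling compares the arms. An article may leave the exact random-effects structure to a fuller document, and the hypotheses concern T2, not a written-out arm-by-time test.

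Most of this stands. A reader might infer that the plan leaves cluster-level variation in change out of the arm comparison; the document does not support that, because it leaves the structure open. A reader might also infer that class movement causes the omission. It does not: whether school variation in change is modelled depends on whether school effects may vary by occasion, whatever happens to classes. And a class that moves up intact makes fixed nesting roughly right for classmates.

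Two things survive. The hierarchy is stated, not merely left open, and it is wrong for teacher and fidelity whichever random effects are chosen. And the safeguards are qualified as applying where practical or in some cases, so none commits the main comparison to cluster variation in change.

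**Conclusion.** The single-class nesting should be corrected: it does not fit repeated measures over two years, and it would misplace fidelity in some years. That part rests on the document alone.

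The effect on the arm comparison is conditional. If school and class are constant intercepts, type I error is roughly 0.11 to 0.5 with 75 matched pupils per school, for school-by-occasion variance of 0.01 to 0.04 or class-by-occasion variance of 0.02 to 0.05. If clusters do not vary in change, it is 0.05. None of these variances is in the document, and the calculation simplifies to two occasions, matched pupils and fully renewed class effects.

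Higher figures should not be read into the plan. With s = 0.04 and e = 0.32, following all 150 pupils gives 0.64, but the plan expects only about half of follow-up surveys to have a matched baseline, and 75 pupils give 0.52. Nor can it be said that false positives would be common, since that requires a model the plan has not chosen. This is something to fix before analysis, not proof that the primary comparison is invalid.

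**What to change.** In the Planned analyses section:

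- Define level 2 as the class attended at each occasion, crossed with child, within school.
- Give school an occasion-specific random effect (unstructured over occasions, or school plus school-by-occasion). Otherwise use a sandwich variance clustered on school, with a small-sample correction, in every arm comparison, the interim one included.
- A simpler alternative is to model the T2 score with baseline covariates and random intercepts for T2 class and school. School-mean baseline suits this, because about half of follow-up surveys will have no matched pupil baseline; state how missing pupil baselines are handled.
- Record a class identifier at each occasion and link fidelity to the class attended that year. The Confidentiality section's list of stored labels does not mention class.

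The cost is one identifier per child per occasion, a few extra variance parameters, and confidence intervals that are wider where schools or classes vary in change, and correct.

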### Randomisation

Randomisation will be carried out by an independent consultant and will be conducted using a computer-generated list of numbers. The allocation will be emailed to the Principal Investigator who will then email individual notifications to schools within a designated timeslot on 1 day. Entire schools will be randomised to the intervention or wait-list control following baseline data collection with stratification by School Management Type and school enrolment size with a 1:1 allocation. This will be achieved as follows:The schools will be sorted by management type and, within management type, by enrolment numbersSchools will be assigned to pairs starting from the top of the sorted list. For example, the two largest catholic maintained schools will be assigned to ‘Pair 1’; the third and fourth largest to ‘Pair 2’ etc.A random number between 0 and 1 will be assigned to each school (the random number being generated within SPSS)Within each of the pairs the school with the smallest random number will be assigned to the intervention group and the other school from the pair will be assigned to the wait-list control group

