### Sample size

The sample size calculation was based on an assumed intra-class correlation coefficient of 0.2, as observed in similar school-based preventative education programmes [29]. The calculation was also based on the primary outcomes of the study, i.e. changes in children’s knowledge, understanding, self-efficacy and proxy skills to keep safe from all forms of abuse. Other studies concerned with preventing sexual abuse that have used a cluster randomised design have reported an average increase of 0.63 standard deviations (ICC = 0.2) for knowledge of sexual abuse concepts, and an average increase of 0.60 standard deviations (ICC = 0.2) for proximal measures of safety skills (i.e. the What If Situations Test) in the intervention group. Programmes with a focus on domestic abuse prevention have reported increases of 0.3–1.3 standard deviations for knowledge of domestic abuse concepts in the intervention group [30]. These studies have also reported an odds ratio of 2.95 in relation to disclosures of abuse [29] while others have reported an odds ratio of 1.10 in relation to reductions in bullying victimisation and perpetration [40].

Power calculations for the current study indicate that approximately 40 schools are required in each arm of the study to detect a minimum detectable effect size of 0.19 standard deviation with 80% power and 95% significance. This will also allow for a minimum detectable percentage point difference of 2.7 for an outcome that is rare in the control group, at around 5% (i.e. disclosure of abuse).

There are several assumptions behind the calculations:The average number of completed surveys per school will be around 150 per timepoint. (The average enrolment number is 200 per school, but the very youngest year groups will not all be included, and amongst older year groups there will be absences);It will prove feasible to track the responses from the same pupils over time. The assumption is that for around 50% of the surveys at follow-up, we will have matched baseline data;For single year group analysis, the average sample size per school will be 30 completed surveys per timepoint;The intra-class correlation coefficient is assumed to be 0.2. This is a value typical for school based studies [29].

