### Child measures

The children’s surveys will consist of a composite of the measures, outlined below, and a number of versions will be used with different age groups. The children’s measures will be administered at each of the three time points.

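### Child survey outcomes have a pre-randomisation baseline, but the plan describes change over three occasions and states no baseline covariate or equal-baseline constraint; a free-baseline change contrast would lose power

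*Protocol article*

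**What the plan says.** The Randomisation section places allocation after baseline: "Entire schools will be randomised to the intervention or wait-list control following baseline data collection". The Child measures section says of the survey scales: "The children’s measures will be administered at each of the three time points".

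The Sample size section describes the primary outcomes as changes in knowledge, understanding, self-efficacy and proxy skills. The Planned analyses section treats the occasions as joint responses in a multivariate model and continues: "At level-1 change in scores across the stages of assessment will be examined within the context of individual variation within and between individuals". Its second route is a structural equation model across the three time points: "A multigroup approach, within the SEM analysis, will be used to test differences across the conditions". Neither route mentions T0 as a covariate or a constraint on the T0 means. The arm contrast itself is not written out. The Discussion frames the child hypotheses at T2.

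On linkage of surveys over time, the Sample size section says: "The assumption is that for around 50% of the surveys at follow-up, we will have matched baseline data".

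**The concern.** Because T0 precedes allocation, any T0 difference between arms is chance. An analysis can use that fact by adjusting for T0 or by holding the T0 means equal across arms. A difference in change with free T0 means does not use it: it subtracts the whole observed T0 gap, although only a fraction R of that gap is expected to persist to T2.

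Two things follow when R is below 1.

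- **Precision.** The change contrast is less precise than the adjusted one, and for R below 0.5 it is less precise than ignoring baseline altogether.
- **Over-correction.** Given an observed T0 gap g, the change contrast is off by -(1-R)g, against the arm that started higher.

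With 40 schools per arm and an ICC of 0.2, nearly all the variance of an arm mean lies between schools. The school's T0 level is therefore among the most useful covariates the trial holds.

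**Working it through.** **Inputs from the Sample size section**

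- Design and target: "approximately 40 schools are required in each arm of the study to detect a minimum detectable effect size of 0.19 standard deviation with 80% power", taken as two-sided 5%.
- "The intra-class correlation coefficient is assumed to be 0.2".
- "The average number of completed surveys per school will be around 150 per timepoint".
- Half of follow-up surveys matched to a baseline survey.

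**Assumed, because the article gives no value:** the school-level T0-T2 correlation ρ (varied below) and a child-level correlation of 0.5. The paired allocation is ignored for both analyses.

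**Step 1: the plan's own figure.** With total variance 1, the variance of a school mean is 0.2 + 0.8/150 = 0.2053. The standard error of a T2-only arm difference is √(2 × 0.2053/40) = 0.1013. The detectable effect at 80% power is (1.960 + 0.842) × 0.1013 = 0.284 SD, not 0.19. Power at 0.19 SD is about 46%. To reach 0.19 from these inputs, the variance must fall to (0.19/0.284)² = 0.448 of its T2-only value. That needs R of about 0.74 with adjustment (1 - R² = 0.448) or about 0.78 with change scores (2(1 - R) = 0.448). Alternatively, an ICC of about 0.085 would give it without any use of baseline.

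**Step 2: variance factors relative to T2-only.** The correlation of school means is

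R = (0.2ρ + 0.8 × 0.5 × 0.5/150) / 0.2053.

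- Difference in change, T0 means free: 2(1 - R).
- Baseline-adjusted: 1 - R².

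The difference is 2(1 - R) - (1 - R²) = (1 - R)², which is positive for every R below 1.

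**Step 3: power at 0.19 SD**, using SE = √(2 × 0.2053 × factor/40) and a noncentral t with 78 df.

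| ρ | R | factor, change | factor, adjusted | power, change | power, adjusted | loss (points) |
|---|---|---|---|---|---|---|
| 0.3 | 0.30 | 1.40 | 0.91 | 34.6% | 49.2% | 15 |
| 0.5 | 0.49 | 1.01 | 0.76 | 45.2% | 56.7% | 11 to 12 |
| 0.7 | 0.69 | 0.62 | 0.53 | 65.0% | 72.3% | 7 |
| 0.8 | 0.79 | 0.43 | 0.38 | 80.8% | 84.9% | 4 |
| 0.9 | 0.88 | 0.23 | 0.22 | 96.9% | 97.7% | under 1 |

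The detectable effects at 80% power (change against adjusted) are 0.34 and 0.27 SD at ρ = 0.3, 0.29 and 0.25 at 0.5, 0.23 and 0.21 at 0.7, and 0.19 and 0.18 at 0.8.

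**Step 4: check with partial matching modelled directly.** A generalised least squares calculation, with matched and unmatched children kept separate and a normal approximation, compares free with equal T0 means. The losses are 13.3, 11.6, 9.7, 7.3, 4.0 and 0.6 points at ρ = 0.4, 0.5, 0.6, 0.7, 0.8 and 0.9. This agrees with Step 3.

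**Step 5: dependence on effect size.** At 0.285 SD and ρ = 0.7 the powers are 94% and 97%, a gap of 3 points. At the 0.60 SD that the article cites from earlier trials, both exceed 99% even at ρ = 0.3.

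**Step 6: size of the over-correction.** The standard error of the chance T0 gap is also 0.1013 SD. For a gap of 0.10 SD and R = 0.49, the change contrast is off by (1 - 0.49) × 0.10 = 0.05 SD.

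**The case against.** **The contrast is not fixed.** A reader might infer that the plan commits itself to a change-score comparison of the arms. It does not. The sentence on change does not mention arm; arm enters only through the multigroup test, with no contrast stated, and the hypotheses are set at T2. The loss arises only if T0 means are free by arm and the test is of T2 minus T0. This objection stands, and the point is conditional for that reason.

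**T0 as a response is not an error.** A reader might take the multivariate treatment of T0 as the fault. It is not: a three-occasion model with equal T0 means uses baseline about as efficiently as covariate adjustment, and the planned model can take that form.

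**It may be analysis-plan detail.** A protocol article may leave such a constraint to the analysis plan. That would answer mere silence. Here, however, the article calls the outcomes changes and sets out how T0 enters, and an analyst following both sections could readily test arm by time with free T0 means. Tests of factorial invariance do not by themselves equate T0 latent means across conditions.

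**Baseline use may have been intended.** The matching assumption, and the fact that 0.19 SD does not follow from the stated inputs without a gain of some kind, are consistent with this. If baseline explains the 0.19, R is about 0.74 to 0.78 and the loss is only about 4 to 6 points. The article does not say so, and a lower ICC would serve equally well.

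**Scope.** A reader might extend the point to every primary outcome. Disclosure comes from school administrative records, and the three-time-point statement covers the child surveys only. New Primary one intakes have no T0 survey of their own.

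**Conclusion.** The point holds for the child survey outcomes, as a conditional one. The article describes change over three occasions with T0 as a response, and states neither a baseline covariate nor an equal-T0 constraint. Should the arm effect be estimated as a difference in change with free T0 means, it is less precise than a baseline-adjusted estimate for every R below 1.

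No single power loss can be read off the plan. The figures rest on an unstated T0-T2 correlation, an assumed child-level correlation of 0.5, and the 0.19 SD target; the loss shrinks as school scores become more stable or effects larger. The matter is worth correcting because the correction is free and the stated inputs leave little power to spare at 0.19 SD. It does not invalidate the design.

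**What to change.** In Planned analyses, state that the T1 and T2 arm effects on child survey outcomes are estimated with T0 means held equal across arms.

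- **Mixed model:** keep all three occasions as responses, with no arm term at T0 and only arm-by-T1 and arm-by-T2 terms. Include a school-by-occasion random effect. A school intercept alone would force a school-level correlation of 1 between occasions.
- **Multigroup SEM:** constrain the T0 latent means to be equal across conditions.

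This keeps children without a matched T0 survey. A follow-up model adjusted for the school's T0 mean is another way to use baseline, but it is a different model, not an equivalent one. Analysis of covariance on the child's own T0 score is not a good substitute: restricted to matched children it would discard about half the follow-up surveys, and with a missing-baseline indicator it would condition on a status that partly reflects events after allocation, such as new intake.

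The Sample size section should also say whether the 0.19 SD assumes a gain from baseline and, if so, at what correlation.

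The cost is a few sentences, with no new data, schools or visits. The packages already named can fit these models.
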